### Data Collection Methods

Baseline and subsequent follow-up rounds will be conducted via structured, interviewer-administered surveys using REDCap tablet-based electronic questionnaires. These instruments have been developed by adapting core modules from the WHO STEPS [30] and the standardized DHS tools of the INDEPTH Network [20], ensuring alignment with established population-based surveillance practice. Household-level forms are linked to each HHID and capture location geocoordinates (imported directly from the mapping module), asset ownership, housing conditions, water and sanitation status, and records of vital events (births, deaths, and in- and out-migrations) since the last round. Individual-level forms are linked via a unique individual identification (INDID) nested within each HHID and address core sociodemographic factors (age, sex, marital status, education level, and occupation), women’s empowerment, and exposure to gender-based violence. Health-related modules capture self-reported history of NCDs (hypertension, diabetes, and cardiovascular disease), mental health status, and key communicable diseases (HIV, tuberculosis, and malaria), as well as reproductive health metrics. For each reported condition, data are also collected on prior diagnosis by a health professional, current treatment status, and type of medication, enabling estimation of the diagnosis-treatment-control cascade for key conditions. Behavioral risk factors assessed include tobacco use, alcohol consumption, dietary patterns, physical activity, and sexual behavior, with skip patterns and range checks built into the electronic tools to minimize data entry errors. All items are drawn from, or adapted directly from, WHO STEPS and INDEPTH Network instruments that have been widely used and validated in demographic and health surveillance sites in sub-Saharan Africa, supporting their reliability and suitability for this target population.

The household questionnaire additionally captures individual-level items on mobile phone ownership (personal or shared), primary connectivity mode (SMS, mobile data, or Wi-Fi), and internet access, providing a baseline characterization of digital access at the household and individual levels to contextualize NCD communication and service delivery in both rural and urban settings.

### Physical and Biochemical Measurements

Standardized physical assessments will be performed by trained nurses or clinical research assistants in accordance with WHO STEPS field measurement protocols using calibrated equipment [30]. These measurements include height, weight, BMI, waist and hip circumference, blood pressure (BP), and heart rate. BP and heart rate are assessed using validated, automated digital sphygmomanometers, which eliminate observer bias and terminal digit preference associated with manual auscultation. Field staff will ensure that participants are seated quietly with their back supported, feet flat on the floor, and arm supported at heart level, using an appropriately sized cuff. Following an initial 5 minutes of seated rest, 3 sequential BP and heart rate readings will be taken at 3-minute intervals. This 5-minute interval strictly adheres to the standardized WHO STEPS protocol for population-based field surveys. Taking 3 measurements allows for the accommodation of transient anxiety or the alerting reaction; the first reading is discarded, and the mean of the second and third readings is used in analyses to provide a reliable estimate of resting BP. To eliminate transcription errors, all readings are documented directly into the REDCap electronic case report forms on the field tablets, which are programmed with automated biological range checks. Height and weight measurements are taken using a stadiometer and digital scale, respectively, calibrated daily, and recorded to the nearest 0.1 cm and 0.1 kg, with height measured in the Frankfort plane. Central obesity is defined by a waist-to-hip ratio exceeding 0.85 in women and 0.95 in men. Biochemical assessments require participants to undergo an 8- to 12-hour overnight fast; finger-stick capillary blood samples are analyzed using point-of-care devices (lipidometers and glucometers) to determine fasting blood glucose, total cholesterol, fasting triglycerides, and high-density lipoprotein. A random spot urine sample (20 mL) is collected for estimation of urinary sodium and creatinine, and, where consent is provided, venous blood samples are taken for further laboratory tests (eg, full blood count and liver function tests). All measurements are recorded directly into the electronic data collection tools and automatically linked to the participant’s INDID.

### Follow-Up Procedures

Following the baseline census, longitudinal data collection rounds will be implemented annually over the 5-year surveillance period. Using the existing household and individual registers, field teams revisit each HHID and reverify the household roster, updating entries for births, deaths, in-migrations, out-migrations, and changes in marital status. Migration events are classified and dated using standard HDSS definitions, enabling calculation of person-time at risk and net migration rates. Migration events are identified and documented during each annual household roster update. New residents found in a previously mapped household who meet the standard residency criterion (at least 3 of the last 6 mo or intending to stay at least 6 mo) are classified as in-migrants, assigned a unique individual ID, and enrolled prospectively, with their origin and date of arrival recorded. Previously enrolled individuals confirmed by household members to have permanently departed the HDSS ward boundaries are classified as out-migrants, with their date of departure, destination, and reason for migration recorded and their follow-up record closed from that date, contributing person-time up to departure. Individuals who return after out-migration are reenrolled under their original ID, ensuring longitudinal continuity.

At each round, eligible adults are recontacted for updated interviews and measurements to estimate NCD prevalence and incidence, monitor changes in health-related behaviors and attitudes, and track risk factors over time. All recorded deaths are subjected to verbal autopsy using the WHO 2016 [31] standardized instrument administered on tablets; data are processed with automated cause-of-death assignment tools (eg, InterVA or InSilicoVA), given the limitations of vital registration in this setting.

Participant retention is managed through a structured recontact protocol whereby temporarily absent individuals receive at least 2 repeat visits at different times before being recorded as noncontactable for that round. At each round, the baseline characteristics of participants lost to follow-up will be compared with those retained to assess and account for potential attrition bias.

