Household mapping is conducted as a structured, multistep process to generate a complete and reproducible sampling frame for longitudinal surveillance. First, existing Enumeration Areas (EAs) from the most recent national census are obtained from the Zimbabwe National Statistics Agency and imported into a GIS platform (QGIS) to delineate EA boundaries for the selected wards. Second, trained field mappers conduct a door-to-door household listing within each EA using handheld GPS-enabled tablets preloaded with custom forms developed in REDCap (Research Electronic Data Capture), recording the precise geographic coordinates of each dwelling, its EA code, and basic dwelling characteristics (eg, structure type and occupancy status). Third, each residential structure that meets the HDSS definition of a household (people who “eat from the same pot” and usually sleep in the dwelling for at least 3 of the last 6 mo) is assigned a unique household identification (HHID) code, which is physically labeled on the dwelling (eg, paint or sticker) and simultaneously captured electronically. Fourth, the georeferenced household list (HHID, EA code, and GPS coordinates) is exported from the data collection platform and integrated into the central HDSS database, where it is linked to the GIS layer to enable spatial checks, duplicate detection, and verification of coverage. The resulting quality-checked household register constitutes the sampling frame for all baseline and follow-up HDSS rounds.

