### Study Population and Sampling

The study population includes all adults aged 18 years and older who are usual residents in the defined rural and urban HDSS areas (ie, the 4 selected wards) at the time of the baseline census. For operational purposes, a “usual resident” is defined as an individual who has lived in the household for at least 3 of the previous 6 months or who intends to stay for at least 6 months, consistent with HDSS standards. As an HDSS, the system aims for exhaustive inclusion of all eligible adults within the mapped households rather than a sample-based design.

Within each mapped household (HHID), fieldworkers use a standardized roster module on the tablet to list all household members, recording name, sex, age, relationship to head of household, and residency status. Adults (aged ≥18 y) who meet the residency criterion and provide informed consent are included and invited to complete individual-level interviews and measurements. Exclusion criteria are (1) individuals younger than 18 years; (2) visitors or short-term guests who do not meet the residency definition; (3) individuals who are unable to provide informed consent and for whom no appropriate consenting procedure is approved; and (4) individuals who explicitly decline participation. For temporarily absent eligible adults (eg, at work or school), at least 2 repeat visits are scheduled at different times and days before classifying them as nonresponders for that round. This approach ensures near-complete coverage of the adult resident population in both communities.

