Within the 4 selected wards, all mapped households constitute the sampling frame, from which a systematic sample of households is drawn. Within each sampled household, all adults aged 18 years and older who meet the residency criterion are identified and invited to participate. Although the HDSS does not enroll every eligible adult resident because of resource constraints, this probability-based household sampling strategy, combined with formal power calculations, ensures that the resulting sample size is sufficient to address the primary study objectives. Using a baseline hypertension prevalence estimate of 30%, consistent with published data from Zimbabwe and comparable sub-Saharan African settings, a margin of error of ±2%, a 95% CI, and a design effect of 1.5 to account for household clustering, a minimum sample of approximately 3000 adults per site is required for robust prevalence estimation. This yields a total minimum analytical sample of 6000 adults across both rural and urban sites.

For the detection of a modest 2% absolute annual change in hypertension or diabetes prevalence (eg, from 30% to 32%) between surveillance rounds, with 80% statistical power and a 2-sided α of .05, a minimum of approximately 3500 participants per site per round is required. The estimated adult population across the 4 HDSS wards substantially exceeds this threshold, supporting the longitudinal objectives of the study. For rural-urban comparative analyses, equal allocation across the 2 sites provides 80% power to detect an absolute difference of 3% to 5% in key NCD outcomes. Subgroup analyses by sex, age group, and socioeconomic stratum are designated as exploratory, and appropriate corrections for multiple comparisons will be applied. Sample size calculations were performed in accordance with the WHO STEPwise approach to NCD risk factor surveillance (WHO STEPS) sample size guidance for population-based NCD surveys.

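### If the household sample governs, in-migrants are enrolled from every mapped household but baseline residents only from sampled ones, so unweighted later-round prevalence can shift

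*Protocol article*

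**What the plan says.** Three parts of the protocol article bear on who enters the panel, meaning the adults interviewed and measured at a round.

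- **Community Profiling and Household Mapping.** Every dwelling that meets the household definition "is assigned a unique household identification (HHID) code". The code therefore belongs to the whole mapped register, not to a sample of it, and that register is the frame for the baseline and for later rounds.
- **Study Population and Sampling.** This section describes the baseline in two incompatible ways. First: "the system aims for exhaustive inclusion of all eligible adults within the mapped households rather than a sample-based design". Later: "all mapped households constitute the sampling frame, from which a systematic sample of households is drawn", followed by "Within each sampled household, all adults aged 18 years and older who meet the residency criterion are identified and invited to participate". It then concedes, "Although the HDSS does not enroll every eligible adult resident because of resource constraints".
- **Follow-Up Procedures.** At each round "field teams revisit each HHID and reverify the household roster". The rule for in-migrants covers "New residents found in a previously mapped household who meet the standard residency criterion"; these people receive an individual ID and are enrolled from then on. Nothing limits this to sampled households.

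The Data Analysis section plans chi-square tests for trend to follow NCD burden over time.

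**The concern.** Read literally, the sampled baseline and the follow-up rule use different sets of households. In a mapped household that was not sampled, a newcomer is enrolled while the long-term residents are not. A resident's chance of entering is f, which is below 1; an in-migrant's is 1.

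The in-migrant share of the panel would then exceed the in-migrant share of the ward population and move further from the baseline mix at each round. If in-migrants have a different prevalence of hypertension or diabetes, an unweighted prevalence would mix a change in panel composition with any real change, and so would a trend test on it. Trend estimation is a main purpose of the surveillance system, and the plan wants to detect a change as small as 2 points between rounds.

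**Working it through.** **Inputs from the article.** Hypertension prevalence 30%, margin of error 2 points, 95% confidence, design effect 1.5, about 3000 adults per site. Bindura: 140,000 people in 14 wards. Two wards per site. Baseline completed in December 2024 (Mt Darwin) and March 2025 (Bindura); first follow-up in the second quarter of 2027; rounds until 2029.

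**The plan's own figure.** 1.96² × 0.30 × 0.70 / 0.02² = 2016.8, and 2016.8 × 1.5 = 3025. This agrees with the stated 3000 or so per site.

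**Assumptions, none of them in the article.**
- 140,000 / 14 = 10,000 people per ward, so about 20,000 in two average wards. Taking roughly half as adults, N = 10,500, and f = 3000 / 10,500 = 0.29. Only Bindura has a ward count; applying it to Mt Darwin is a further assumption.
- In- and out-migration are balanced at 5% per year.
- Time since baseline is about 2.4 years at the first follow-up (December 2024 to mid second quarter 2027) and 4.4 years at the 2029 round.
- Every in-migrant arrives in a mapped household.

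**Model.** With u = exp(−0.05t):
- baseline residents still present: 3000u
- in-migrants, mapped-household rule: 10,500(1 − u)
- in-migrants, sampled-household rule: 3000(1 − u), a panel share of 1 − u, equal to the population share

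| | 2.4 years | 4.4 years |
|---|---|---|
| u | 0.887 | 0.803 |
| Residents | 2661 | 2408 |
| In-migrants, mapped rule | 1187 | 2074 |
| Share, mapped rule | 1187/3848 = 31% | 2074/4482 = 46% |
| Share, sampled rule | 11% | 20% |
| Excess share | 0.196 | 0.265 |

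**Shift in unweighted prevalence** = excess share × (in-migrant prevalence − resident prevalence):

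| Prevalence gap | 2.4 years | 4.4 years |
|---|---|---|
| 0 points | 0 | 0 |
| 5 points | about 1.0 | about 1.3 |
| 10 points | about 2.0 | about 2.7 |

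The shift is downward if in-migrants have the lower prevalence and upward if they have the higher. Over 7000 to 14,000 adults per site, 2% to 8% yearly migration and gaps of 5 to 10 points, its absolute size runs from 0.3 to 3.2 points at 2.4 years and from 0.5 to 3.7 at 4.4 years. With no gap it is 0 throughout.

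These shifts are cumulative from baseline. Between 2.4 and 4.4 years, the 10-point gap adds 2.7 − 2.0 = 0.7 points, or about 0.35 per year.

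**Does weighting remove it?** Take f = 0.27, a true in-migrant share of 10%, resident prevalence 30% and in-migrant prevalence 20%. The true value is 0.9 × 0.30 + 0.1 × 0.20 = 29.0%.
- Unweighted: (0.27 × 0.9 × 0.30 + 0.1 × 0.20) / (0.27 × 0.9 + 0.1) = 0.0929 / 0.343 = 27.1%.
- Residents weighted 1/f, in-migrants 1: (0.0729 / 0.27 + 0.02) / (0.9 + 0.1) = 29.0%.

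Weighting by each person's own inclusion probability restores the true value.

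**The case against.** The strongest reply is that the mismatch derives from the unresolved contradiction about the baseline. Follow-Up Procedures speaks of a baseline census and of re-verifying rosters, which is the language of exhaustive inclusion. If that description governs, f is 1 and the shift is exactly zero. This stands, and it makes the point conditional. It does not dispose of it: the Abstract describes a multistage sampling design, the sampling text cites limited resources, and settling the matter in favour of the sample would still leave the word mapped in the in-migrant rule.

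Second, enrolment in that rule may mean demographic registration only. The sentence sits among roster and person-time matters and sets no age limit, and measurement comes in the next paragraph. This reading is possible. However, that paragraph covers eligible adults without restricting them to sampled households, and a field team could reasonably follow the literal wording.

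Third, weights may be specified in a full protocol or analysis plan that is not shown. That is fair: the absence of weights from an article is no fault in itself. The point concerns the enrolment rule that the article does state.

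A reader might infer more than the documents support:
- *That prevalence will drift.* The article gives no sampling fraction, migration rate or migrant prevalence. Drift needs both a prevalence gap and an unweighted analysis, and its direction is unknown.
- *That the drift matches the 2-point change the plan targets.* That target is annual, between rounds; the 2-point shift is cumulative over 2.4 years and needs the larger, 10-point gap.
- *That the rural-urban contrast is distorted.* No site-specific migration figure supports this.

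The model may also overstate the in-migrant share, because people settling in dwellings built after mapping have no stated route into the panel.

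**Conclusion.** The point holds conditionally. If the household sample governs, the follow-up wording gives in-migrants to mapped households an inclusion probability of 1 against f for baseline residents, and over-represents them in later rounds. If inclusion is exhaustive, there is no problem. Under the assumed inputs, in-migrants are 31% of the panel at 2.4 years where a sampled-household rule would give 11%. An unweighted prevalence then moves by about 1 point for a 5-point gap and 2 points for a 10-point gap, cumulatively and in either direction, and not at all if in-migrants have the same prevalence. That is enough to complicate interpretation of the trend test, and it should be settled before the first follow-up round in 2027.

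**What to change.** 1. Reconcile the two descriptions of baseline inclusion in Study Population and Sampling, and state which one governs.
2. If the sample governs, reword the in-migrant rule in Follow-Up Procedures so that in-migrants are enrolled for interview and measurement only in sampled households. Mapped households outside the sample would receive at most a roster update.
3. If in-migrants of unsampled households are to be measured, record each household's sampling status. In prevalence and trend estimates, weight each person by the inverse of that person's own inclusion probability: 1/f for baseline residents and 1 for in-migrants. A single household-level weight would not do, because the two groups can share a household.

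The cost is small: a wording change made before any follow-up fieldwork. Under step 2 fewer in-migrants are measured, which reduces fieldwork but leaves fewer of them for migrant-specific analyses. Step 3 keeps those numbers but requires sampling status to be recorded and a weighted analysis.

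### In-migration is defined at the household and out-migration at the ward boundary, so a move between households inside the wards counts as an entry with no exit and biases net migration upward

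*Protocol article*

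**What the plan says.** All the migration rules are in the protocol article, Methods, Follow-Up Procedures.

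- **Purpose.** "Migration events are classified and dated using standard HDSS definitions, enabling calculation of person-time at risk and net migration rates".
- **Entry.** "New residents found in a previously mapped household who meet the standard residency criterion" "are classified as in-migrants, assigned a unique individual ID, and enrolled prospectively, with their origin and date of arrival recorded". The test is applied at the household. Origin is recorded but plays no part in the classification.
- **Exit.** "Previously enrolled individuals confirmed by household members to have permanently departed the HDSS ward boundaries are classified as out-migrants", with "their follow-up record closed from that date, contributing person-time up to departure". The test is applied at the ward boundary and needs a household member to confirm it.
- **Return.** "Individuals who return after out-migration are reenrolled under their original ID, ensuring longitudinal continuity".

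Two other sections bear on the point. Under Data Collection Methods, "Individual-level forms are linked via a unique individual identification (INDID) nested within each HHID". Under Study Population and Sampling, "all mapped households constitute the sampling frame, from which a systematic sample of households is drawn", although the same section also states an aim of exhaustive inclusion.

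No rule is printed for an enrolled adult who moves from one household to another inside the wards.

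**The concern.** A net migration rate is entries minus exits over person-time, so both must be counted across the same line. Here they are not, and the error runs one way: internal moves can add entries but never exits.

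Three features add to the problem.

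- The rule preserving a person's ID is limited to those who come back after out-migration. An internal mover has not out-migrated under the printed definition.
- The individual ID is described as nested in the household ID, and the identity check at follow-up visits (Data Management and Quality Assurance) uses the household ID, which changes with a move.
- When a whole household leaves, no member remains to confirm the departure.

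Migration is among the determinants the article sets out to compare between sites, and the limitations expect more mobility in urban and periurban populations. If internal moves are commoner in Bindura than in Mt Darwin, the error would not cancel in the rural-urban comparison. Baseline ended in December 2024 (rural) and March 2025 (urban), and the first follow-up is planned for the second quarter of 2027. About 25 to 30 months of moves will therefore be classified in one round.

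**Working it through.** The article states no migration rate, internal-move rate or person-time total, so there is no figure to reproduce. The check applies the printed rules and then sizes the result under labelled assumptions.

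**Step 1. The rules applied to each kind of move**

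| Move | Entry recorded | Exit recorded | Correct ward-level net |
|---|---|---|---|
| Outside the wards to a followed household | +1 | 0 | +1 |
| Followed household to outside the wards | 0 | 1 | -1 |
| Followed to followed, same ward | +1 | 0 | 0 |
| Unfollowed to followed, same ward | +1 | 0 | 0 |
| Followed to unfollowed, same ward | 0 | 0 | 0, but no rule ends the record |

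The first two rows are right. The third and fourth each give a spurious +1. The last two rows arise only if households are sampled; the third arises under sampling or full enumeration.

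A move between two of the four study wards is ambiguous. If the boundary is each ward separately, it gives one exit and one entry. If it is the four wards taken together, even a Mt Darwin to Bindura move gives an entry without an exit.

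**Step 2. Size of the net migration error**

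Inputs:
- N = 3000 adults per site (the article's minimum for prevalence estimation; used for scale only).
- m = share of adults changing household within the wards each year. Not in the article; assumed 1% to 10%.
- Steady state, with recorded origin not used to reclassify.

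Spurious entries per year = N × m:
- m = 1%: 3000 × 0.01 = 30
- m = 5%: 3000 × 0.05 = 150
- m = 10%: 3000 × 0.10 = 300

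Error in the rate = (N × m) / N = m, that is +1, +5 and +10 per 100 person-years. N cancels. The share of households followed does not enter either, because arrivals from followed and unfollowed households are both miscounted.

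**Step 3. Person-time, conditional on two failures**

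This applies only if a mover between followed households gets a second ID that is never linked, and the old record stays open to the end. Let f be the share of households followed (not in the article; assumed 0.25 to 1.0) and T = 5 years (the stated surveillance period). Moves spread evenly leave the old record open for T/2 years on average:

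excess / true = (N × m × f × T²/2) / (N × T) = m × f × T/2

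- m = 1%, f = 0.25: 0.01 × 0.25 × 2.5 = 0.6%
- m = 5%, f = 0.5: 0.05 × 0.5 × 2.5 = 6.25%
- m = 10%, f = 1: 0.10 × 1 × 2.5 = 25%

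If the records are linked, this excess is 0, but the error in Step 2 remains unless the move is also reclassified. Movers to unfollowed households are not in this figure; their person-time depends on a censoring rule that the article does not give.

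**Step 4. After the fix**

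With one boundary, or an internal-move event that keeps the ID, a move within the wards adds 0 to net migration and 0 excess person-time.

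**The case against.** The strongest reply is that this is a condensed article. It invokes standard HDSS definitions, says that operating procedures cover every step, and promises them as annexes; coding of internal moves could well be there. Safeguards are also described: origin and arrival date for each in-migrant, server scripts to find duplicates, and an identity register of name, date of birth and sex. Net migration is not among the outcomes used to size the study, and no follow-up data exist yet.

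Much of this stands, and it rules out two stronger readings.

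- A reader might infer that every internal mover is given a second ID. The article says a unique ID is assigned; it does not say that someone already enrolled gets another. The nesting and the narrow return rule make a second ID plausible, not certain.
- A reader might also infer that person-time is inflated and that incidence and mortality are understated. That needs both failed linkage and an old record left open. The article has a noncontactable status and compares those lost with those retained; when such records are censored may properly be settled in an analysis plan.

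What does not stand is the appeal to standard definitions as a cure for the entry and exit rules. The article prints both rules in specific terms after the general phrase, and they use different boundaries. Nor is it stated that recorded origin changes the classification, or how duplicates are matched. Field staff have no access to the identity register.

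**Conclusion.** The mismatch is in the text and needs correcting. As written, the rules bias the net migration rate upward by the internal-move rate unless moves are reclassified from recorded origin. That rate is not in the documents; over an assumed 1% to 10% a year the error is +1 to +10 per 100 person-years, which restates the assumption and is not a forecast.

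Duplicate IDs are a risk, not a stated consequence. Overstated person-time (0.6% to 25% over five years across the assumed ranges) holds only if records go unlinked and uncensored. The article supplies no ward adult population or sampling fraction, so the number of adults affected cannot be derived from it. Prevalence estimates are not put in question by this point. No follow-up round has begun, so nothing has yet been miscounted.

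**What to change.** Before the first follow-up round:

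1. Define entry and exit against the same boundary, and state whether that is each ward or all four wards together.
2. Add an internal-move event, identified from recorded origin and destination, that closes the old household episode, keeps the person's individual ID and counts as neither in- nor out-migration.
3. Make the individual ID independent of the household ID, with household membership held as a dated episode.
4. Have the data manager match new arrivals centrally against the identity register before an ID is confirmed. A search by fieldworkers would conflict with the register's access restriction.
5. Where no household member can confirm a departure, censor at the last confirmed contact.

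The cost is a changed event form and ID rule, a central matching step in each round, and some less exact exit dates. No additional household visits are needed.
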